### 2.2. Study Location

The study will be carried out in the Physical Medicine and Rehabilitation Service of the Teresa Herrera Maternal and Child Hospital of the A Coruña and Cee Health Area. Further sites may be joining the recruitment once their approvals are finalized. The study will be conducted between January 2024 and December 2024 in the Physical Medicine and Rehabilitation Service of the Teresa Herrera Maternal and Child Hospital of the A Coruña and Cee Health Area.

The data collected will pertain to subjects at risk of neurological alteration or diagnosis of cerebral palsy or neuromotor disease, who are admitted for assessment and/or physiotherapy treatment. Following the usual clinical practice protocol, the children will be assigned to one of the physiotherapists who apply Vojta therapy (patients who will be considered as the intervention group) or to a physiotherapist who applies conventional treatment (patients who will be considered as the control group).

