### 2.3. Participants

Participant selection allows the randomization of the sample following the natural ordering of the rehabilitation service where the study is carried out. The assignment of children to their different therapists is performed according to the available treatment times of the latter. In other words, patients are assigned to one treatment or another following criteria of immediacy as part of the regular routine of the rehabilitation service. Therefore, the randomization will be carried out through the needs of the service, as is already the case.

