### Statistical Methods

Statistical analysis will be performed using the SPSS 27.0 statistical software for Windows (SPSS Inc., Chicago, IL, USA; version 27.0). The normality of the sample will be checked using the Shapiro–Wilk test, and if it follows a normal distribution, an analysis of variance (ANOVA) of repeated measures p will be used, with time (pre-treatment and post-treatment) as an intra-group factor, and Vojta and conventional physiotherapy groups as the inter-group factor, all with a Bonferroni correction. Statistical analysis will be performed with a confidence level of 95%, so a *p*-value of <0.05 will be considered significant.

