## 4. Discussion and Ethical–Legal Aspects

Completed assessment data of four subjects has been collected to date, as two subjects withdrew prematurely or did not sign the consent form. Recruitment is currently ongoing at our first site and no results report is available due to the small sample. 

The baseline scoring of GMFM at initial assessment is related to the age of the child in order to understand the rate of items acquisition so far. The aim of this study is not to compare absolute values of GMFM between different subjects according to their age and, therefore, if the children are born preterm, the chronological age is considered. This allows us to plot changes due to spontaneous and therapeutic gross motor experience after birth. 

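### If further sites join with different Vojta shares, the planned ANOVA, which has no site term, can mix site differences in change into the treatment effect

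*Protocol article*

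**What the plan says.** Section 2.2 (Study Location) names one rehabilitation service and then adds: "Further sites may be joining the recruitment once their approvals are finalized". Section 4 describes the current state in the same spirit: "Recruitment is currently ongoing at our first site". It reports complete assessments for four children, against 30 planned per group.

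Arm is decided by local staffing. Section 2.3 states: "The assignment of children to their different therapists is performed according to the available treatment times of the latter". Sections 2.1, 2.2 and 3 describe the same mechanism: a child taken on by a Vojta therapist is in the intervention group, and a child taken on by a conventional therapist is a control. No ratio per site and no balancing within site is given.

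Statistical Methods names the factors of the model. The ANOVA is to be run "with time (pre-treatment and post-treatment) as an intra-group factor", with "Vojta and conventional physiotherapy groups as the inter-group factor, all with a Bonferroni correction". Site does not appear. Section 2.5 lists geographic background as a recorded variable but does not place it in the model.

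**The concern.** Under randomization stratified by site, arm and site are unrelated by design, and leaving site out of the model mainly costs precision. Here the share of children receiving Vojta at a site is that site's mix of therapist time. Nothing keeps this share the same from one site to the next, so site can predict arm. Site can also predict how much a child changes over two months, through age at referral, severity, frequency of clinic contact or local unblinded GMFM assessment. When both hold, a pooled comparison of arms is partly a comparison of sites.

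This goes beyond a detail that an article leaves to a fuller document. One section opens the trial to more sites and another fixes a two-factor model, and the two do not fit together once a second site contributes.

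**Working it through.** **Inputs from the protocol article.** 30 children per arm (section 2.6; taken as given, its justification is a separate matter). Factors time and group only, with significance at p < 0.05 (Statistical Methods; two-sided assumed).

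**Inputs not in the document, therefore assumed.** Two sites, no true treatment effect, a site difference in pre-to-post change *D* of 0.5 to 0.8 SD of change, and the split of each arm between sites. The plan gives no figure of its own on this point to reproduce.

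**Step 1: what the model tests.** With two time points, the group × time test equals a two-sample t-test on change. The relevant site difference is therefore the difference in change.

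**Step 2: bias.** Let *a* of the 30 Vojta children and *b* of the 30 conventional children come from site 2. Then

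bias = *D* × (*a* − *b*) / 30.

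- 20 and 10: (20 − 10)/30 = 0.333, so the bias is 0.17 SD at *D* = 0.5 and 0.27 SD at *D* = 0.8.
- Vojta shares of 70% and 30% at two sites of 30, that is 21 and 9: (21 − 9)/30 = 0.4, so the bias is 0.20 SD and 0.32 SD.
- 15 and 15: zero.

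**Step 3: false positives by simulation.**

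| Split *a*/*b* | Site difference | Bias (SD) | False positives, no site term | With site in model of change |
|---|---|---|---|---|
| 15/15 | 0.5 in change | 0 | 4.1% | 4.9% |
| 18/12 | 0.5 in change | 0.10 | 5.6% | 4.8% |
| 20/10 | 0.5 in change | 0.17 | 8.8% | 5.0% |
| 20/10 | 0.8 in change | 0.27 | 14.2% | 4.9% |
| 21/9 | 0.5 in change | 0.20 | 11.1% | 5.1% |
| 21/9 | 0.8 in change | 0.32 | 18.9% | 5.6% |
| 20/10 | 0.8 in level only | 0 | 5.0% | 5.2% |

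The 21/9 rows used 5,000 simulated trials; a repeat with 10,000 gave 10.4% and 18.5% without a site term. The other rows used 10,000. All rates are at 0.05 for a single outcome. A stricter threshold from the Bonferroni correction would lower the percentages but leave the bias unchanged.

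**Step 4: the limiting case.** If each site supplied only one arm (*a* = 30, *b* = 0), the bias would be the whole of *D*. A site term could not help, because site and arm would be the same variable.

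**The case against.** A reader might infer that site differences are already being counted as treatment effect. The document does not support that. Further sites are only a possibility, none is named, and one service is described throughout. With one site there is nothing to confound.

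A reader might also infer that opening more sites is enough to cause bias. It is not: the Vojta shares must differ as well, and no text shows that they will. An 18/12 split barely moves the error rate. Splits of 80/20 (19% to 40% false positives over the same range of *D*) or a Vojta-only second site (24% to 49%) give alarming figures, but the document supports neither, and sections 2.1 and 2.2 describe a service with both kinds of therapist.

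The pre-post design is a real protection. A site whose scores are shifted equally at both visits contributes nothing to group × time, as the last row of the table shows. One limit applies. Section 2.6 says rates, not net scores, will be analysed, and the second calculation in section 4 takes the pre-intervention rate as the whole baseline score over two months. A constant offset *L* in the score leaves score change untouched, since (S1 + L) − (S0 + L) = S1 − S0. It raises that pre-intervention monthly rate by *L*/2 and leaves the post rate, (S1 − S0)/2, alone. So a constant difference in score is not a constant difference in that rate.

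Section 4 also plans to examine the influence of age, GMFCS level, follow-up frequency and other factors, and the IMP is scored by a blinded external assessor. These narrow the routes by which site could matter, but they do not put site into the comparison of arms.

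**Conclusion.** The point holds conditionally. Three things must coincide: further sites contribute children, their Vojta shares differ, and they differ in change on the analysed measure. The allocation method makes unequal shares plausible, and the stated model offers no protection if they occur. For moderately unequal shares (20/10 to 21/9) and an assumed site difference in change of 0.5 to 0.8 SD, the bias is about 0.17 to 0.32 SD and the false-positive rate about 9% to 19% instead of 5%. These sizes illustrate the mechanism; the document gives no site split, site difference or SD from which to predict them.

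**What to change.** In Statistical Methods, state that if a second site contributes children, the ANOVA includes site and site × time; equivalently, that site is a fixed factor in the model of change. A site main effect alone does not adjust the group × time contrast, so the interaction with time must be named. In section 2.2, state that only sites with study children in both arms over the same period inform the comparison of arms.

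The cost is about one degree of freedom per added site, and single-method sites do not contribute to the comparison. Some precision is also lost when shares differ. For the 20/10 split the correlation of arm with site is 0.333, so the standard error grows by √(1/(1 − 0.333²)) = 1.06; for 21/9 it grows by √(1/(1 − 0.4²)) = 1.09, for the same residual SD.

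The change is best made before a second site opens. Deciding on adjustment once data are in would be data-dependent, and complete overlap of site and arm could not be repaired. The change does not cure the non-random allocation within a site, which is a separate issue.

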### 2.3. Participants

Participant selection allows the randomization of the sample following the natural ordering of the rehabilitation service where the study is carried out. The assignment of children to their different therapists is performed according to the available treatment times of the latter. In other words, patients are assigned to one treatment or another following criteria of immediacy as part of the regular routine of the rehabilitation service. Therefore, the randomization will be carried out through the needs of the service, as is already the case.

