# Effects of Vojta Therapy on the Motor Function of Children with Neuromotor Disorders: Study Protocol for a Randomized Controlled Trial

**DOI:** 10.3390/jcm12237373

**Published:** 2023-11-28

**Keywords:** cerebral palsy, Vojta therapy, neuromotor disorder, neurorehabilitation, brain injury

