## Abstract

Background: Infantile cerebral palsy is a neurological pathology that causes great morbidity, mortality, and disability in people who suffer from it, mainly affecting motor development. There are a multitude of non-pharmacological methods or therapies for its treatment. One of the main methods is Vojta therapy. This methodology acts on ontogenetic postural function and automatic postural control. Objective: This study aims to demonstrate that there are changes in the motor development of children with cerebral palsy with the application of Vojta therapy. Methods and analysis: This is a randomized controlled trial on the effectiveness of two neurorehabilitation techniques in patients with cerebral palsy conducted at the Physical Medicine and Rehabilitation Service of the Teresa Herrera Maternal and Child Hospital of the A Coruña and Cee Health Area. The study will be conducted from January 2023 to December 2024. There will be two groups: the Vojta therapy group (*n* = 30) and the conventional physiotherapy group (*n* = 30). The measurement variables will be gross motor function as measured by the Gross Motor Function Measure (GMFM) and Infant Motor Profile (IMP) scales. Ethics and dissemination: The study was approved by the Research Ethics Committee of the University of Murcia (1823/2018) and Comité de Ética de la Investigación de A Coruña-Ferrol (2022/099). Trial registration number: ClinicalTrials.gov; identifier: NCT06092619.

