For this reason, studies involving intervention with Vojta therapy, which follows these same principles, also seem to demonstrate its effectiveness in these aspects. VT is a commonly extended tool in the field of pediatric rehabilitation [6,20]. Numerous studies have reported improvements in the acquisition of sitting in infantile cerebral palsy [21], gait acquisition [20,22], improving gait kinetics and kinematics [23,24,25], as well as stability, trunk balance, and spinal symmetry [26,27]. Furthermore, Vojta therapy is considered to be one of the most recommended techniques for the treatment of respiratory disorders in infantile cerebral palsy [28]; it has proven to be the technique of choice in respiratory physiotherapy as it has been shown to improve compliance, SO2, and SpO2 by reducing the respiratory frequency without increasing PCO2 [29,30,31]. Furthermore, previous research showed how VT accelerates the acquisition of GMFM-88 items and locomotor stages in children with cerebral palsy younger than 18 months by activating the postural control required to achieve the uncompleted items. This work pointed to the need to develop future studies analyzing the effects of VT at different treatment dosing, with blind assessments and larger samples [6]. Previous studies described significant differences in GMFM sitting after VT, even if the total score of the GMFM-88 did not [21]. VT has been reported to be clinically beneficial for strength, movement, and motor activities in individual cases [32] and is being considered within the second of three levels of evidence in interventions for cerebral palsy [33]. Poor study design has cast a shadow over the positive results in previous studies about VT, including a lack of random sequence generation, concealed allocation, study blinding, incomplete outcome data collection, and selective reporting [33]. On the other hand, a randomized controlled trial showed improvements in postural control and motor function early rehabilitation of adults with acute stroke [34,35]. The ethical limitations of randomized untreated control groups or placebo interventions limit the quality of the intervention in this field. Baseless attributed child distress [33] has been found in the literature [36,37,38], and bonding facilitation due to an integrative approach of the family in the rehabilitation process has also been described [37]. Family participation in the decision-making process is highly emphasized [39], and its integration on the therapeutic handling reduces economic cost and commuting times and increases the dosing possibilities. 

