## 2. Materials and Methods

### 2.1. Study Design

A pseudo-randomized clinical trial has been designed that will assess gross motor function before the physiotherapy intervention (with Vojta therapy or conventional physiotherapy intervention, such as environmental enrichment and task-specific training) and two months after its application. The clinical trial has been conducted according to the consolidated standards of reporting trials (CONSORT) statement [40]. The current treatment protocol is described according to the recommendations of SPIRIT [41].

Patients are assigned to one treatment or another following criteria of immediacy as part of the regular routine of the rehabilitation service. Therefore, the randomization of the sample is possible following the natural ordering of the rehabilitation service where the study is carried out. The participants in this research, within their care routine and according to the health protocols established in the service, will be assigned to one of the two study groups:Intervention group: patients under Vojta Therapy intervention [17,18,19,20,21,22,23,24,25,26,27,28]Control group: patients under regular physiotherapy intervention, such as environmental enrichment and task-specific training [25]

This methodology will be useful to provide a service evaluation of the operation of the rehabilitation service itself.

Neither the therapists nor the evaluators of the GMFM may be blinded to the type of treatment administered due to the organization of the rehabilitation service where the study is carried out, as well as the “face-to-face” requirements for carrying out the Vojta therapy and the evaluation of that scale. However, the assessment of the Infant Motor Profile (IMP) is performed by observing a protocolized video recording. This allows the quantification of this factor by an evaluator external to the service (in this case the external principal investigator). This will not only allow us to blind the evaluator regarding the type of intervention that the child receives, but also whether the video belongs to pre- or post-intervention groups. To do this, the videos will be sent after being encrypted and randomized for quantification. 

The study was approved by the Research Ethics Committee of the University of Murcia (1823/2018) and Comité de Ética de la Investigación de A Coruña-Ferrol (2022/099). This trial has been registered under the following code: ClinicalTrials.gov Identifier: NCT0609261.

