## 3. Methods and Timeline

Phase 1. Initial Assessment: Children who go to the rehabilitation center where they have been referred will be treated, an initial routine clinical examination will be performed, including: Personal/medical data collection.GMFM quantification.Treatment with the physiotherapist.Training of the parents in the home program.Recording for the IMP quantification.

Phase 2. Intervention period (2 months): The assignment to the therapist will be randomized according to the needs of the service, where each therapist will adapt the treatment according to the initial assessment. Both assessors and therapist cannot be blinded to the allocation or treatment, and both required live-direct performance. An external assessor (blind to both) will be able to score the IMP recordings. 

Children will receive weekly or fortnightly treatment, and their parents, family members, or carer will be trained in carrying out a home program. Each therapist will adapt the treatment according to the initial evaluation, as is usually performed in the rehabilitation service. During the treatment sessions, the physiotherapist will apply the therapy directly, either based on Vojta therapy or conventional physiotherapy. The frequency of repetition of the treatment at home and in the hospital will be recorded, depending on the availability of each family and the normal functioning of the service.

Phase 3. Second assessment at 2 months (±1 week, depending on follow up appointments).

Collection of data on the possible changes made in previous treatments and the frequency of home treatment (possible incidents due to illness or family limitations).GMFM quantification.Recording necessary for IMP quantification.

Children carried on clinically with the intervention, but this short period would allow us to attribute changes to RL, controlling better the influence of other factor (such as age maturation or other therapy inputs).

Study length. The data collection will be carried out for 4 years from the approval of the CEI. Only patients receiving healthcare with any of the therapies under investigation after authorization by the CEI will be included.

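### The study is labelled randomized, but arms are formed by therapist availability, and the between-group test names no covariate

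*Protocol article*

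**What the plan says.** **Label.** The title reads "Study Protocol for a Randomized Controlled Trial", and the abstract states "This is a randomized controlled trial on the effectiveness of two neurorehabilitation techniques in patients with cerebral palsy". Section 2.1 opens differently: "A pseudo-randomized clinical trial has been designed". It then claims CONSORT conduct and says that the sample can be randomized through the service's natural ordering. Section 3 (Phase 2) returns to the stronger word: "The assignment to the therapist will be randomized according to the needs of the service".

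**Mechanism.** Section 2.3 explains how a child reaches a therapist: "The assignment of children to their different therapists is performed according to the available treatment times of the latter". It restates this as: "patients are assigned to one treatment or another following criteria of immediacy as part of the regular routine of the rehabilitation service". It adds that this is how the service already works. Section 2.2 completes the link: a child given a Vojta physiotherapist is in the intervention group, and a child given a conventional physiotherapist is in the control group.

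**Background.** The Introduction lists the design faults of earlier Vojta studies, "including a lack of random sequence generation, concealed allocation, study blinding, incomplete outcome data collection, and selective reporting".

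**Analysis and inference.** The Statistical Methods subsection of Section 3 plans a repeated-measures ANOVA with time as the within-group factor and treatment as the between-group factor, at a 5% level. It names no covariate. Section 3 says that the short period allows changes to be attributed to reflex locomotion. Section 4 says that a confirmed hypothesis would make Vojta therapy the key to gross motor development.

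**The concern.** Random allocation justifies reading a between-group difference as a treatment effect and taking the p-value at face value. Here the arm follows from whichever therapist has time. Nothing in that process is drawn by chance. Because the free slot identifies the therapist and the therapist identifies the arm, there is no step at which the arm could be concealed.

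The article states this mechanism positively, so it is not a detail left to a fuller protocol or an analysis plan. A random sequence supplied elsewhere would contradict this text.

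What is at stake is the kind of conclusion the trial can support. If the slot a child receives depends on age, severity or the family's availability, each of which plausibly bears on motor gain over two months, the arms differ before treatment starts. The planned test would then mix that difference with the treatment effect. The protocol would also repeat two of the faults it gives as reasons for doubting earlier work.

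**Working it through.** **1. The label against the mechanism**

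| Place | What it says about allocation |
|---|---|
| Title, abstract | Randomized controlled trial |
| Section 2.1 | Pseudo-randomized; assignment by immediacy in routine care |
| Section 2.2 | Therapist's method defines the arm |
| Section 2.3 | Therapists' free time; service needs; called randomization |
| Section 3, Phase 2 | Randomized according to service needs |

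The mechanism is the same wherever it is described, and it contains no chance element. The label differs between places, and only Section 2.1 qualifies it.

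**2. Does comparing each child with itself protect the between-group test?**

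Section 2.3.2 argues that children are compared only with themselves. Section 4 defines the comparison: the pre-intervention rate is score divided by age, and the intervention-period rate counts only new points over the two months. Let G(a) be the score at age a in months. With no treatment effect, the change in rate is

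[G(a+2) − G(a)]/2 − G(a)/a.

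- If growth were linear from zero, this would be 0 at every age.
- Sections 2.6 and 4 say growth is not linear. As an assumed example, take G(a) = k·a². Then G(a+2) − G(a) = k(4a+4), and the change in rate is k(2a+2) − k·a = k(a+2).
- The expected change therefore rises with age without any treatment effect. A gap of D months in mean age between arms gives a spurious between-arm difference of k·D.
- Section 4's second calculation puts all earlier items in the last two months, so the pre-rate is G(a)/2. The change is then k(4a+4−a²)/2, which also depends on age.
- If the rate were total score over age at both visits, the change would be k(a+2) − k·a = 2k, free of age. Section 4 does not define the intervention-period rate that way.

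Self-comparison therefore removes some differences between children, but not differences in expected gain.

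**3. Effect on the error rate, under assumed imbalance**

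The plan states no imbalance, so there is no figure to reproduce. The inputs from the documents are 30 per group (Section 2.6) and a two-sided 5% level (Statistical Methods). The systematic prognostic difference b, in SD units of the analysed change, is assumed.

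- Standard error of the between-arm difference: √(2/30) = 0.258 SD.
- Rejection probability with no treatment effect: 1 − Φ(1.96 − b/0.258) + Φ(−1.96 − b/0.258).

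| b (SD) | b/0.258 | Rejection under the null |
|---|---|---|
| 0 | 0 | 5.0% |
| 0.1 | 0.39 | 6.7% |
| 0.2 | 0.77 | 12.1% |
| 0.3 | 1.16 | 21.3% |
| 0.5 | 1.94 | 49.1% |

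**The case against.** The strongest reply is that the mechanism is disclosed. Section 2.1 says pseudo-randomized, Section 2.3 describes the booking openly, and Section 2.1 also presents the study as a service evaluation. A careful reader of the Methods is not misled. That stands as mitigation, but the title, abstract, Section 2.3 and Section 3 still claim randomization.

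A second reply is that availability may be unrelated to prognosis. This also stands. Section 2.3 names only therapist time and service needs, and nothing shows that age, severity or urgency determines the slot. A reader might infer that the 5% error rate necessarily fails. The documents support only that it may.

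A third reply is that covariates are not ignored. Section 2.3.2 says concomitant treatments will be considered in the calculations, and Section 4 intends to examine the influence of GMFCS, age and prior therapy. Details may sit in an analysis plan that is not shown. But the model that the article does state contains only time and group.

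Other stronger readings should be resisted:

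- Section 2.3.1 could be read as saying that referral by method decides the arm. The sentence can equally just name the service's two treatment streams, and Sections 2.2 and 2.3 describe assignment by availability.
- No passage says who books or what that person knows. Foreknowledge of the arm is plausible but not stated.
- Section 4 says there are no results to report, so the criticism concerns the planned description and inference, not a published claim.

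**Conclusion.** The point stands as a mismatch between label and design that affects the planned inference. Allocation as described is non-random and cannot be concealed, the document contradicts itself on what to call it, and the stated between-group model has no covariate to offset a difference between arms.

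How much bias results is unknown. The figures of about 12%, 21% and 49% rest on assumed systematic differences of 0.2, 0.3 and 0.5 SD, a normal approximation, 30 per arm and no adjustment. With no systematic difference the rate stays at 5%. The need to correct the label does not depend on these figures.

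**What to change.** **Main change (wording and analysis only).**

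- Describe the study as a non-randomised (quasi-experimental) controlled comparison in the title, abstract and Sections 2.1, 2.3 and 3. The registry record was not available, so nothing is said about its wording.
- Limit the causal statements in Sections 3 and 4 to what such a comparison can support.
- Make the primary between-group analysis adjust for age, GMFCS level, baseline score and prior therapy. Sections 2.5, 3 and 4 show that all of these are already collected.

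The cost is a less favourable label and some degrees of freedom. With 60 children in two groups, a comparison of change has 60 − 2 = 58 residual degrees of freedom. Age (1), five GMFCS levels (4), baseline score (1) and prior therapy as one term (1) use 7, leaving 51. Adjustment handles measured factors only, so it does not restore the randomized label.

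**Alternative for future children.** If the service can use a concealed computer-generated list held outside it, the randomized label could apply to children allocated that way and to no others. This costs more than the list itself:

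- Consent in Section 2.3.1 is described as permission to use data, so consent and ethics approval would probably need changing.
- Phase 1 in Section 3 places treatment and parent training inside the initial assessment, so allocation would have to be placed after the baseline measurements.
- Children already allocated by availability should be analysed separately. Section 4 reports complete data for four, so there were few of these at the time of writing.
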